### Consent

For this trial we will employ three tiers of consent: state, Panchayat, and individual.

• At the state level, approval of the protocol has been obtained from the Department of Health & Family Welfare of the government of Andhra Pradesh.

• Consent will also be obtained from each Panchayat in the trial area. The Panchayat is a democratically elected body that governs a small group of villages. This is the smallest unit of government in rural India. In all villages in the trial, consent will be obtained from the Panchayat in the following manner. These local bodies will convene their general body meetings (also called the Gram Sabhas). The protocol of the trial will be explained to the villagers in their local language. Consent will be given in oral form during a Panchayat meeting with written documentation of the approval given by the Panchayat leader. This process of obtaining consent through meetings with approval of the 'guardians' of the clusters is common in trials in which the intervention is delivered at the level of a cluster and it is not possible to obtained for informed consent for randomisation from individuals within the cluster [22].

• Given this process, women who are asked and agree to take part in the enumeration are considered to have given their informed consent to participate in the trial. Women not living in the villages at that point who subsequently fulfil the eligibility criteria will be informed about the study and asked if they agree to be added to the list.

### Sample size calculation

The sample size has been calculated to give 80% statistical power to show a reduction in neonatal mortality that is statistically significant using a conventional 2-sided significance level of 5% if the true effect of the package of interventions is to reduce neonatal mortality by 25%. We assumed 4.38% neonatal mortality in the control villages (and hence 3.29% neonatal mortality in the intervention villages), an average population of 659 per village, a birth rate of 23 per 1000 population (giving rise to an average of 38 births per village over a period of 2.5 years) and an intra-cluster correlation coefficient of 0.00644 [20,6]. Under these assumptions we require 330 villages to detect a 25% reduction in neonatal mortality.

In the trial area, however, women who are expecting their first child usually move back to their mother's village around one to three months before the expected date of delivery. This migration could reduce the measured effect of intervention if women move from control villages to intervention villages and vice-versa. According to the NFHS-2, 36% of all births are first births in Andhra Pradesh. We assume that 90% of these women temporarily migrate and on the basis of this that 8% of control women actually deliver in an intervention village, whilst 24% of intervention women will deliver in non-intervention villages (8% in control group villages and 16% in villages outside of the study area) [20]. Assuming that both groups incur half the benefits of the intervention, the expected neonatal mortality rates in the two groups become 4.34% and 3.42%. Under this scenario 464 villages will still give 80% statistical power to show a reduction in neonatal mortality that is statistically significant at the 5% level.

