Thanda	Administratively, a thanda refers to a hamlet with a small population (around 100 households) vis-à-vis 'villages'. Each thanda is considered a part of a nearby village although the two habitations could be distant from each other.
Penta	A Tribal Chenchu village is known as a "penta". Each penta consists of few huts that are spaced apart and are grouped together based on kinship pattern. The close relatives live nearby and the distant ones farther away. Their homes comprise of few belongings and are generally sparse and Spartan in appearance.
Anganwadi Worker	Angan literally means "courtyard." Under the Integrated Child Development Services Scheme, there is an Anganwadi worker for each population of 1000 people. She is selected from the community and undergoes training in various aspects of health, nutrition and child development. She is a part time worker and is paid an honorarium for service including health checkups, immunisation, supplementary nutrition, health education, and informal preschool education and referral services for women in general and children below the age of 6 years.
DALYs	Disability Adjusted Life Years is the sum of years of potential life lost due to premature mortality and the years of productive life lost due to disability.
Gram Sabha	An assembly of all the adults of a given village which meets at least twice in a year. The Gram Sabha considers proposals for taxation, discusses annual programmes and elects members of the Gram Panchayat.

The methods for implementing this programme are also derived from the public health literature. There is a growing body of evidence showing the potential efficacy of community interventions to address public health problems and disseminate health knowledge, however there exists a large research gap in the literature evaluating such interventions [4-7,3]. Similarly, contracting out of health service provision to non-public enterprises appears promising, yet is also under-researched [8-11]. Our study looks to investigate the potential of these two types of intervention in tandem and in the context of the Lancet Neonatal Survival Series findings [2].

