### Randomisation

Villages will be stratified according to whether their travel time to the nearest designated NPHC is less or greater than one hour, and also into three groups according to whether the village is thanda (2–3 km from the main village with around 15 families), penta (20–30 km from the main village with around 4–5 families) or non-tribal (a main village). All villages will be randomly allocated, within each of these six strata, to either the intervention or control group.

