### Enrolment – Trial site(s) and participants

The trial site is the Nagarkurnool division of Mahabubnagar district in the Indian state of Andhra Pradesh. The trial will involve only those villages in the division with a population of less than 2,500 people. This criterion was decided upon in light of the fact that larger villages and towns generally have better access to health services, lower neonatal mortality rates, and therefore less potential to benefit from the interventions. Under this criterion, a total of 464 villages will be eligible for the trial with a total population of approximately 300,000 people.

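### The 80% power stated for the migration scenario assumes villages of equal size and is probably a few points too high

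*Protocol article*

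**What the plan says.** The section on sample size opens with the claim "The sample size has been calculated to give 80% statistical power" for a 25% reduction, two-sided at 5%. It continues: "We assumed 4.38% neonatal mortality in the control villages (and hence 3.29% neonatal mortality in the intervention villages". Cluster size enters only as a mean: 659 people and a birth rate of 23 per 1000, "giving rise to an average of 38 births per village over a period of 2.5 years". The ICC is 0.00644. These inputs give 330 villages. After an allowance for women who move to deliver, the expected rates become 4.34% and 3.42%, and the section says that 464 villages retain 80% power.

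Elsewhere the article describes the clusters. The Randomisation section stratifies them into main villages, thandas ("km from the main village with around 15 families") and pentas of about 4–5 families, each randomised as a unit. The section on trial site and participants sets only an upper limit: "The trial will involve only those villages in the division with a population of less than 2,500 people". All 464 eligible villages are used. The glossary gives a different thanda size: "a thanda refers to a hamlet with a small population (around 100 households".

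The primary analysis is an unadjusted generalised linear model with robust standard errors.

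**The concern.** When cluster sizes vary and the analysis pools births within each arm, large villages carry more of the weight and the variance exceeds what the equal-cluster design effect allows for. The power section mentions only the average. At 23 per 1000 over 2.5 years, and assuming 5 people per family (not in the article), a penta would yield about 1 birth, a 15-family thanda about 4, and a village at the size limit about 144.

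At stake is the power quoted for the scenario that justifies using 464 villages rather than 330. If it is overstated, the steering committee and readers plan on a type II error of 20% when the true figure is somewhat larger. No eligible villages remain in the division to make up the difference.

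**Working it through.** **Inputs from the sample size section.** Two-sided 5%, power 80%; rates 4.38% and 3.29% (no migration), 4.34% and 3.42% (migration); m = 38 births per village (659 × 0.023 × 2.5 = 37.9); ICC 0.00644. The allocation is 1:1, so 232 villages per arm.

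**Migration rates.** Control: 4.38% × (1 − 0.08 × 0.125) = 4.34%. Intervention: 4.38% × (0.76 × 0.75 + 0.24 × 0.875) = 3.42%. Both agree with the article.

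**Reproducing 330 and 464.** Births per arm without clustering, with p̄ the mean of the two rates:

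n = [1.96√(2p̄(1−p̄)) + 0.842√(p1(1−p1) + p2(1−p2))]² / (p1−p2)²

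Continuity-corrected: n_c = (n/4)[1 + √(1 + 4/(n|p1−p2|))]²

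Equal-cluster design effect: 1 + (38 − 1) × 0.00644 = 1.238. Villages in total = 2 × births per arm × 1.238 / 38.

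- No migration: n = 4,872, n_c = 5,054. Villages: 318 uncorrected, 329.4 corrected (stated 330).
- Migration: n = 6,916, n_c = 7,132. Villages: 451 uncorrected, 464.8 corrected (stated 464).

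The match to both totals with the corrected formula and a design effect of 1.238 indicates that no term for size variation was included.

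**Allowing for unequal villages.** Design effect = 1 + [(1 + CV²) × 38 − 1] × 0.00644, where CV is the coefficient of variation of births per village. Effective births per arm = 232 × 38 / design effect; the formulas above are then solved for power.

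Example at CV 0.9: design effect = 1 + (1.81 × 38 − 1) × 0.00644 = 1.437; effective births = 8,816 / 1.437, about 6,137 per arm. Uncorrected, z = (√6,137 × 0.0092 − 1.96 × 0.2731) / 0.2730 = 0.68, which is 75.1% power.

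| CV (assumed) | Design effect | Power with correction | Power without |
|---|---|---|---|
| 0 | 1.238 | 79.9% | 81.1% |
| 0.5 | 1.299 | 77.9% | 79.2% |
| 0.7 | 1.358 | 76.1% | 77.5% |
| 0.9 | 1.437 | 73.6% | 75.1% |
| 1.0 | 1.483 | 72.2% | 73.8% |

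Without the correction, 80% holds only up to a CV of about 0.37.

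**Check by simulation.** Beta-binomial data, crude log relative risk with a cluster-robust standard error, 6,000 runs per setting: 82% power with equal villages, 79% at CV 0.52, 76% at 0.79 and 75% at 0.94.

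**Plausible CV.** If 15% of villages had 75 people and all others were identical, with the mean at 659, the CV would be (584/659) × √(0.15/0.85) = 0.37. For an assumed mix of 20% thandas, 5% pentas and main villages with CV 0.4–0.6 among themselves, the overall CV is 0.69–0.85 if a thanda has 75 people (15 families of 5) and about 0.47–0.64 if it has 500 (100 households of 5).

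**Detectable reduction.** Scaling the planned 25% by √(design effect / 1.238) gives 25.6% at CV 0.5 and 26.9% at CV 0.9.

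**Undiluted effect.** For 4.38% against 3.29% at 464 villages and CV 1.0, power is 86.2% with the correction and 87.2% without.

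**The case against.** The decisive input is missing from the article. It does not give the CV, the number of thandas and pentas, or the spread among main villages. The 2,500 is an eligibility limit, not an observed village. This stands: the size of the shortfall is conditional on an assumption, and a flat statement that 80% power is not achieved would go too far.

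A reader might also infer that the plan has no margin at all, since the reproduced requirement is 464.8, or 465 villages, even at CV 0. The article does not support that. It names no formula; the continuity correction is inferred from the match. The correction is conservative and is not part of the planned robust-standard-error analysis. Without it, equal villages give 81.1% power, and the simulation gives 82%. The fraction above 464 comes from rounding in the inputs.

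Nor is this an arithmetic slip. The stated totals follow from the stated averages; what fails is the unstated assumption of equal sizes.

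Finally, the consequence is limited. The ICC is small, no design decision changes, and the main result will be reported as a relative risk with a 95% confidence interval, from which precision can be read directly. So a reader who infers that a null result would necessarily be over-interpreted is also going beyond the documents. All of this bears on the size of the point. It does not remove the mismatch between an equal-cluster calculation and the range of village sizes that the article itself describes.

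**Conclusion.** The point holds with moderate weight. The power quoted for the migration scenario rests on villages of equal size, and the article's own strata and size limit make that assumption untenable. For CV 0.5–0.9, power at 464 villages is roughly 74–79%, depending on the CV and on whether a continuity correction is used. Retaining 80% without the correction needs a CV of at most about 0.37, which is hard to reconcile with units ranging from a handful of families to nearly 2,500 people. Both thanda sizes, under the mix assumed above, give a CV beyond that limit.

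The result rests on an assumed CV, on the article's ICC and mean births, and on an analysis that pools births within arms. It concerns only the migration-diluted effect.

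**What to change.** Keep the 464 villages. Compute the CV of village population, or of expected births, from the list of villages to which the 2,500 limit was applied. Put it into 1 + [(1 + CV²) × 38 − 1] × 0.00644, and say whether a continuity correction is used. Then restate in the sample size section either the power in the migration scenario (roughly 74–79% for CV 0.5–0.9) or the reduction detectable with 80% power (about 25.6–27% rather than 25%).

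Reconcile the thanda size between the Randomisation section (about 15 families) and the glossary (around 100 households), because it affects the CV.

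The cost is one short calculation from data that the trial team should already hold, a rewritten sentence and a slightly less favourable figure. No extra villages or data collection are needed.

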### Analysis strategies

The main analysis will assess the effect of the interventions on the primary and secondary outcomes. Primary analysis of the outcome(s) will follow the intention to treat principle (i.e. the participants will remain in the group they were randomised to and not analysed according to the interventions actually received), and will account for clustering.

For the primary outcome (neonatal mortality), the relative risk with a 95% confidence interval will be reported, taking appropriate account of clustering. A generalised linear model (without adjustment for covariates) using robust standard error estimates will be used to carry out this analysis. A further analysis will adjust for distance to nearest healthcare centres (public and private) and migration.

For secondary binary outcomes, including neonatal morbidity, maternal mortality and morbidity, and health service usage, relative risks will be estimated in an analogous fashion. For continuous outcomes t-tests with robust SEs will be carried out. ANCOVA (with robust standard errors) will be used where baseline adjustment is required. Bootstrapping will be used for non-normal outcomes and Cox models for survival analysis. A full analysis plan is given in the operations manual.

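### The primary model leaves out the six randomisation strata; to the extent that they predict neonatal mortality, its standard error is too large and available precision is forgone

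*Protocol article*

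**What the plan says.** The Randomisation section of the protocol article crosses travel time to the nearest designated non-public health centre (below or above one hour) with village type (thanda, penta or non-tribal), and then states: "All villages will be randomly allocated, within each of these six strata, to either the intervention or control group".

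The Analysis strategies section fixes the primary analysis of neonatal mortality as a relative risk with a 95% confidence interval, allowing for clustering: "A generalised linear model (without adjustment for covariates) using robust standard error estimates will be used to carry out this analysis". It adds one adjusted analysis of this outcome: "A further analysis will adjust for distance to nearest healthcare centres (public and private) and migration". That list includes distance, which is close to the travel-time factor, but not village type.

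The Sample size calculation section makes no allowance for stratification. It uses an intra-cluster correlation of 0.00644 with no part assigned to the strata.

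**The concern.** Stratified allocation balances the arms on the strata, so differences in mortality between strata largely drop out of the true sampling variance of the relative risk. A robust standard error clustered on village, taken from a model without the strata, still counts those differences as noise. Clustering on village does not correct this, because the excess variation lies between strata.

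The article gives some reason to think that the strata are prognostic. The section on the trial area says that rates in rural and tribal regions are believed to be higher, and lists distance from care among the obstacles to reducing mortality. The section on trial sites excludes larger villages because they have better access and lower mortality. If that is right, the primary interval will be wider than the design justifies, and the balance obtained at randomisation will not be used in the analysis.

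**Working it through.** **Inputs, all from Sample size calculation.** Two-sided 5% level and 80% power. Before migration: "We assumed 4.38% neonatal mortality in the control villages (and hence 3.29% neonatal mortality in the intervention villages". After migration the rates are 4.34% and 3.42%. For cluster size: "giving rise to an average of 38 births per village over a period of 2.5 years" (659 × 0.023 × 2.5 = 37.9). The intra-cluster correlation is 0.00644. The stated numbers of villages are 330 before and 464 after allowing for migration.

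**Reproducing the plan's figures.**
- Design effect: 1 + (38 − 1) × 0.00644 = 1.238.
- Before migration: 5,054 births per arm with continuity correction. 5,054 × 1.238 / 38 = 164.7, so 165 per arm and 330 in all, an exact match (318 without the correction).
- Diluted rates: 4.38 − 0.08 × 0.5 × 1.09 = 4.34 and 3.29 + 0.24 × 0.5 × 1.09 = 3.42, as stated.
- After migration: 466 villages with the correction and 452 without, against the stated 464.
- Power at 464 villages, without the correction: the effective number per arm is 232 × 38 / 1.238 = 7,120, and z = (0.0092 × √7,120 − 1.96 × 0.2731) / 0.2730 = 0.883, which gives 81.1%. With the correction it is 79.8%.

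**Effect of adding the strata.** Let f be the share of between-village variance that the strata explain. The article does not give it, so I assume a range of 0 to 50%. The design effect becomes 1 + 37 × 0.00644 × (1 − f), and the ratio r of adjusted to unadjusted standard error is the square root of that value over 1.238. The last column is the power of the unadjusted test when the strata do explain f: its standard error stays at the f = 0 value but the true spread shrinks by r, so power is Φ(0.883 / r).

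| f | Design effect | r | Power, strata in model | Rise over 81.13% | Power, strata left out |
|---|---|---|---|---|---|
| 0 | 1.238 | 1.000 | 81.13% | 0 | 81.13% |
| 10% | 1.215 | 0.990 | 81.87% | 0.7 | 81.4% |
| 25% | 1.179 | 0.976 | 82.99% | 1.9 | 81.7% |
| 50% | 1.119 | 0.951 | 84.85% | 3.7 | 82.3% |

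With continuity correction, power with the strata in the model is 79.8%, 81.8% and 83.8% at shares of 0, 25% and 50%. The rise over the planning figure is thus 0 to about 4 points. Part of it reaches the unadjusted test anyway, through the balance. Comparing the two models directly, the difference is about 0.5, 1.3 and 2.5 points at 10%, 25% and 50%.

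**Check by simulation** (4,000 trials per scenario, stratified allocation, beta-binomial deaths, log-link model with village-robust variance, six strata of equal size).
- Strata carrying about 19% of between-village variance: power 80.6% without and 82.0% with the strata; type I error 5.1% and 5.7%.
- Strata carrying about 86%, beyond the range assumed above: mean unadjusted standard error under the null 0.079 against a true standard deviation of 0.071; type I error 2.7% and 4.7%; power 83.4% and 87.6%.
- The average estimate and its true spread were practically the same with and without the strata, so the cost lies in the standard error and not in the estimator.

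**The case against.** The strongest reply is that the loss is conditional and may be small. The Randomisation section gives no reason for the strata, which may serve logistics as much as prognosis, and the article itself calls the tribal evidence anecdotal. Large shares need large contrasts. The between-village standard deviation is √(0.00644 × 0.0434 × 0.9566) = 1.64 percentage points. For one evenly split binary factor, a 25% share therefore needs about 3.5% against 5.2% mortality, and a 50% share about 3.2% against 5.5%. Pentas have 4 to 5 families and may hold few births. Thandas are less certain: the Randomisation section gives around 15 families and the glossary around 100 households. This stands, and it is why the range has to start at zero. At modest shares the simulation shows no clear conservatism: 5.1% is within Monte Carlo error of 5% (standard error about 0.34 points).

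A reader might also infer that the interval is certainly too wide, or that the trial gives away power it cannot spare because 464 is both every eligible village and the number required. The article does not support either. No prognostic strength is given, and the planned 80% takes no credit for stratification, so it already describes an unadjusted analysis.

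Two further replies carry less weight. The distance adjustment partly covers the travel-time factor, but only in a secondary analysis and without village type. The full analysis plan in the operations manual is not shown, but the article itself fixes the primary model as unadjusted, so this is a stated choice and not an omission.

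**Conclusion.** The mismatch between design and primary analysis is real. The unadjusted analysis is valid, unbiased for the relative risk and at worst conservative; what it forgoes is extra precision. Over an assumed 0 to 50% share of between-village variance, the standard error is 0 to 5% larger than it need be, and power at 464 villages could stand 0 to about 4 points above the planning figure: about 1 point at 10%, 2 at 25% and 4 at 50%, with the direct difference between the two models somewhat smaller. If the strata are not prognostic, there is no loss. These figures rest on the protocol's rates, cluster size and intra-cluster correlation, on equal village sizes, and on a variance share that the protocol does not give. The change is worth making because it is nearly free, not because the planned analysis fails.

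**What to change.** Make the primary analysis the same log-link generalised linear model with village-clustered robust standard errors, plus the stratification factors: travel-time category and village type. Settle the handling of sparse penta strata in advance and without reference to outcomes, for example by combining penta with thanda or by using main effects only. A rule triggered by the absence of deaths in a stratum would make the primary model depend on the results. Report the unadjusted relative risk as a sensitivity analysis.

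The cost is one sentence in Analysis strategies and a matching line in the full analysis plan. No new data are needed, because both factors are known at randomisation. The model spends at most five parameters among 464 villages, or three with main effects only. The change should be made before any outcome data are analysed by allocation, including the first interim analysis, so that it cannot look driven by the results.
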